### Intervention facilitators

Sessions will be administered by two mindfulness instructors with more than ten years of expertise with validated mindfulness-based interventions. The two instructors will receive specific training to deliver the Be.M® Program for the study population. During the intervention, they will receive constant support of a trained pediatrician and they will be encouraged to share their experiences in a regular basis. The whole intervention will be supervised by the study investigators.

### Implementation outcomes

#### Feasibility

The primary outcome of this study is feasibility, which is an implementation outcome that reflects the extent to which a new treatment can be successfully carried out in a specific setting. Typically, this outcome is retrospectively measured by recruitment, retention and participation rates. Feasibility is the most important outcome to be assessed when organizations and providers try new treatments [35]. The feasibility of our study will be evaluated based on the recruitment, retention, and participation rates over one year of study. The success of feasibility will be determine by a recruitment rate of 30 patients in 1 year of study with a retention and participation rate of at least 10%.

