### Data analysis

As this is a pilot feasibility trial, a sample size calculation is not appropriate. Given time and logistical constraints, our aim is to recruit as much patients as possible over a 1-year period. A sample of 40 participants recruited is expected to achieve the goal of 30 participants who complete the study, which may be sufficient to provide useful information about the feasibility of the protocol [46, 47].

Baseline data on all enrolled patients will be summarized using descriptive statistics. Feasibility will be analyzed to compare all eligible patients with those enrolled and those who completed the program with complete measurements collected. Fidelity will be classified according to the score measured by the implementation form.

Comparison tests of two means will be performed on the DASS 21 score. The comparisons will be made with ANOVA repeated measures analysis or with the non-parametric equivalents as appropriate. The descriptive and inferential statistics will be two-tailed, will be reported with 95% confidence intervals and will use *p* values at an α = 0.05 level of significance.

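### The feasibility success rule attaches 30 to patients recruited, the data analysis section attaches 30 to completers, and the rule can be met well short of the completer goal

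*Protocol article*

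**What the plan says.** Feasibility is the primary outcome, judged on recruitment, retention and participation over one year. The Feasibility section (under Implementation outcomes) sets the success rule in one sentence with two parts: "a recruitment rate of 30 patients in 1 year of study" and "with a retention and participation rate of at least 10" per cent.

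The Data analysis section says that for a pilot "a sample size calculation is not appropriate" and that "our aim is to recruit as much patients as possible over a 1-year period". It then gives a planning expectation: "A sample of 40 participants recruited is expected to achieve the goal of 30 participants who complete the study". It adds, in cautious terms, that this may be enough to inform on feasibility. The same section says that feasibility will be analysed by comparing eligible patients with those enrolled and with those who finished the programme with full measurements.

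Neither section refers to the other's figures.

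**The concern.** The number 30 does two jobs. In the Feasibility section it counts patients recruited; in the Data analysis section it counts patients who complete. A reader cannot tell which one the team will hold itself to.

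The success rule decides the primary conclusion. As printed, a year that ends well below the stated completer goal would be reported as feasible, and the article says that the study is to serve as a model for a later efficacy trial. A declaration of feasibility that rests on few completers would carry into the planning of that trial.

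**Working it through.** **Inputs**

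- Success threshold for recruitment: 30 in 1 year (Feasibility).
- Success threshold for retention and participation: 10% (Feasibility).
- Expected number recruited: 40 (Data analysis).
- Completer goal: 30 (Data analysis).
- Working definition: retention = completers ÷ recruited. The article gives no formula, so this is an assumption.

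**Step 1. The plan's own figure.** Implied retention = 30 ÷ 40 = 0.75, so implied dropout = 0.25. Going back, 30 ÷ (1 − 0.25) = 40. The figure reproduces, but only because the rate was derived from the same two numbers. This shows internal consistency and is not independent support for 75%.

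**Step 2. Completers when the success rule is just met or recruitment is raised.** Completers = recruited × retention.

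| Recruited | Retention | Completers | Goal |
|---|---|---|---|
| 30 | 75% (implied) | 22.5 | 30 |
| 30 | 10% (floor) | 3 | 30 |
| 40 | 75% (implied) | 30 | 30 |
| 40 | 10% (floor) | 4 | 30 |

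At 30 recruited and 75% retention the shortfall is 30 − 22.5 = 7.5 completers, or 25% of the goal. At the floor it is 27 of 30, or 90%. Raising the recruitment mark to 40 and leaving the floor at 10% would still allow success with 4 completers. The retention clause is therefore the larger source of the gap.

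**Step 3. Could 30 recruits deliver 30 completers?** Only with 100% retention. Treating participants as independent, the probability is 0.75^30 = 0.0002 at the implied rate. At assumed higher rates it is 0.90^30 = 0.04 and 0.95^30 = 0.21.

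**Step 4. How a joint rule would behave.** Suppose success required both 40 enrolled and 30 completing. With exactly 40 enrolled and true retention of 75%, the exact binomial probability of 30 or more completers is 0.58. A trial running as planned would miss the rule about 42% of the time (1 − 0.58). This bears on the choice of remedy.

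**Step 5. Could the Feasibility figure mean completers?** The sentence calls it recruitment and sets retention separately. If it did mean 30 completers from the expected 40, retention would already be 75% and a 10% clause would add nothing. The sections do not fit together on that reading either.

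**The case against.** The best defence is that a minimum for declaring feasibility may properly sit below the number a team hopes to reach. On that view 30 recruited is a floor, the 40 and 30 are a planning expectation, and nothing is contradicted. The principle stands. But the article does not present the figures as a floor and a target: one section defines success, the other names "the goal of 30 participants who complete the study", and no text relates them. If a tiered rule was meant, it has to be stated.

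Some of the defence stands in full and limits the point. No sum in the article is wrong. The 25% attrition is implied and nowhere stated. The Data analysis section already describes 30 of 40 as expected, so the 58% figure corrects nothing that it claims. No passage requires 100% retention, so Step 3 only shows how far apart the two uses of 30 lie.

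A reader might infer that 40 recruits or 30 completers are needed, and that a smaller study would be uninformative. The documents do not support this. They decline a sample size calculation, leave recruitment open-ended within the year, and call 30 completers possibly sufficient, which is not the same as necessary.

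That this is a condensed article does not answer the point, because both sets of figures are printed and it is their disagreement that is at issue.

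**Conclusion.** The point holds as a mismatch between the primary success rule and the stated completer goal. The rule can be met with about 22–23 completers at the implied 75% retention, or with as few as 3 at the 10% floor, against a goal of 30.

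The 22–23 rests on the back-calculated 75%; the 3 rests on reading retention as completers divided by recruited. With another denominator the 3 would change, but the use of 30 for two different quantities would not.

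It would go too far to conclude that the sample is inadequate, or that the trial falls short of a fixed enrolment quota, since the article sets no such quota. It would also be incomplete to blame the recruitment mark alone, because the 10% clause accounts for most of the distance. The consequence is confined to what a declaration of feasibility would mean, but that is the trial's main conclusion.

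**What to change.** Use one set of numbers in the Feasibility and Data analysis sections, and say in both whether each figure counts patients enrolled or patients completing. Either of two routes would do.

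1. **Define success by the stated goal.** Success is 30 participants completing with post-test data within the 1-year period. Keep 40 enrolled as the planning expectation and not as a second hurdle, so that 30 completers from fewer than 40 enrolled still counts. If exactly 40 enrol and retention is 75%, the chance of reaching 30 is still only 0.58 (Step 4); the open-ended recruitment leaves room to enrol more.
2. **Keep 30 enrolled as an explicit minimum.** State that it implies about 22–23 completers at 75% retention, and bring the 10% threshold into line with the 75% implied in the Data analysis section. If a margin below 75% is wanted, state it with the number of completers it allows.

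Neither route adds procedures or a fixed enrolment requirement. The cost is a stricter primary criterion or a less favourable stated yield. The article describes the study as already being conducted and as retrospectively registered, so the change alters a primary success threshold in a running study. It should be dated and justified, and should say how much recruitment and retention data the team had seen when it was made.

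### The primary success rule accepts 10% retention and participation, far below the 30 completers out of 40 that the protocol itself expects

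*Protocol article*

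**What the plan says.** Under Implementation outcomes, Feasibility, the protocol article states: "The primary outcome of this study is feasibility". The outcome is to be judged on recruitment, retention and participation. Success is defined as "a recruitment rate of 30 patients in 1 year of study" together with a second condition, "with a retention and participation rate of at least 10" percent. Neither retention nor participation is given a denominator there, and no reason is given for the figure.

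The Data analysis section declines a formal calculation ("As this is a pilot feasibility trial, a sample size calculation is not appropriate") but gives a planning expectation: "A sample of 40 participants recruited is expected to achieve the goal of 30 participants who complete the study". It describes that number of completers as possibly enough to learn something useful about feasibility. On the analysis it says: "Feasibility will be analyzed to compare all eligible patients with those enrolled and those who completed the program with complete measurements collected". That sentence names three groups but does not say which of them forms the denominator of each rate.

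The implementation form (Table 2, under Fidelity) records for each patient the number of sessions missed, from 0 to 8 (item 11), and whether the programme was finished (item 12).

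**The concern.** The minimum result that counts as success and the result the study is planned around differ by a factor of seven or more: 10% against an implied 75%. A trial that just passes on retention would have 3 or 4 completers, where the goal is 30. Nothing in the article explains the gap.

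One figure also serves two different quantities. Retention usually means staying to the end; participation usually means how much of the programme was attended. A single 10% cannot be a considered floor for both.

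At stake is the main conclusion of the pilot. The abstract says the evidence should be useful to clinicians and policymakers and that the study should serve as a model for a later efficacy trial. The Discussion also concedes that the extra effort made during the study may inflate retention and participation, so a lenient bar is easier still to clear. At the minimum passing result, the exploratory before-and-after DASS-21 comparison could rest on 3 or 4 patients.

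**Working it through.** **Inputs.** Recruitment threshold 30 and retention/participation threshold 10% (Feasibility); 40 recruited and 30 completing (Data analysis); 8 sessions (Design overview). Assumption: retention = completers / enrolled, the usual meaning, which the article does not state.

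**The plan's own figure.** Implied completion = 30 / 40 = 0.75. In reverse, 30 / (1 − 0.25) = 40, which matches the stated 40. This shows only that the pair is arithmetically consistent, because the 75% is derived from the same two numbers.

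**Minimum that passes on retention.** 0.10 × 30 = 3 completers, 27 lost. 0.10 × 40 = 4 completers, 36 lost. In both cases 90% are lost.

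**Chance of passing the retention part.** With X ~ Binomial(n, p), P(pass) = P(X ≥ 3) for n = 30 and P(X ≥ 4) for n = 40. For example, with n = 30 and p = 0.20: 1 − [0.8^30 + 30(0.2)(0.8^29) + 435(0.2^2)(0.8^28)] = 1 − [0.0012 + 0.0093 + 0.0337] = 0.956.

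| True retention | n = 30 (3 needed) | n = 40 (4 needed) |
|---|---|---|
| 5% | 0.19 | 0.14 |
| 10% | 0.59 | 0.58 |
| 15% | 0.85 | 0.87 |
| 20% | 0.96 | 0.97 |
| 25% | 0.99 | >0.99 |

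**Distance between floor and expectation.** Exact (Clopper-Pearson) 95% intervals: 3/30, 2.1% to 26.5%; 4/40, 2.8% to 23.7%; 30/40, 58.8% to 87.3%. The intervals around the minimum passing results do not overlap the interval around the expected one.

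**Participation.** If it means the share of sessions attended, 10% of 8 is 0.8 of a session. A patient who attends one session, which could be the introductory one, has 1/8 = 12.5% and is above the floor.

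**Recruitment part.** The threshold of 30 recruits equals the goal of 30 completers. At the implied 75%, 30 recruits give 30 × 0.75 = 22.5 completers. The rule can therefore be met while the goal is missed, even if retention is as expected.

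**Alternative readings of 10%.** As a maximum loss, it would require 36 of 40 to stay, more than the 30 the protocol expects, so the two sections would still disagree. As completers over eligible patients, 30 completers would be 10% of 300 eligible; the article gives no number of eligible patients, so this cannot be checked.

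**The case against.** The strongest reply is that an expected result and a minimum acceptable result are different things. A floor should lie below the expectation, so 10% and 30 of 40 are not a strict contradiction. The 75% is never stated as a retention rate, and the protocol expressly disclaims a sample size calculation. This stands: the two figures can coexist logically, and it would be wrong to say that a calculation rests on 75%. It does not explain why the floor is so far below the expectation, or how 3 or 4 completers would meet the purpose for which 30 were wanted.

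The denominator is also open. Because the feasibility analysis starts from all eligible patients, a rate over eligible patients cannot be ruled out, nor can a slip for maximum loss. This stands as a limit on the 90% loss figure, but either explanation means that the sentence needs correcting.

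A reader might go further and infer three things that the article does not support:

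- That this is the trial's only decision threshold. The same sentence sets a recruitment threshold, and fidelity has cut-offs at 40% and 70%.
- That the rule cannot discriminate at all. At a true 5% it passes only 14% to 19% of the time, so it does discriminate, but at a level too low to be of use.
- That passing triggers an efficacy trial. The Discussion presents the larger trial as a future idea, shaped by whatever adaptations the pilot suggests, and ties no progression decision to the 10%.

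**Conclusion.** The point holds: the retention and participation floor in the primary success rule is far too low and is not reconciled with the protocol's own expectation. Followed as written, the rule lets a programme that loses about 90% of enrolled patients satisfy the retention condition, and one with true retention of 20% would satisfy it 96% to 97% of the time.

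These probabilities concern the retention part only. They are not the probability of overall success, which also needs 30 recruits and 10% participation; neither enters the calculation. They assume completers over enrolled as the rate, 30 or 40 enrolled, and independent patients with a common probability of completing.

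This is a badly fixed threshold for the primary outcome, not a detail left to a fuller document. A fuller document could define the denominators, but it could not make a 10% floor on enrolled patients fit a goal of 30 completers out of 40.

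**What to change.** Amend the Feasibility section as follows and bring the Data analysis section into line.

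1. State the numerator and denominator of each rate. For retention, use completers over enrolled patients.
2. Replace the 10% with a retention criterion set below, but consistent with, the expected 30 of 40, and give its operating characteristics. For illustration only, at least 24 of 40 would be reached with probability 0.99 if true retention is 75%, 0.57 if 60%, 0.13 if 50% and under 0.01 if 40%. The 60% cut has no source in the article; the investigators should choose and justify their own. Using 30 of 40 itself as the bar is not advisable: a programme with true retention of exactly 75% reaches it with probability 0.58 and so misses it 42% of the time.
3. Set a separate participation criterion based on the share of the 8 sessions attended. The sessions-missed item on the implementation form already supplies the data.
4. Report both rates with 95% confidence intervals.
5. If 10% was intended as a maximum loss or as a share of eligible patients, say so and correct the sentence.

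The cost is more than an edit. The Study setting section says that the study is being conducted, and registration was retrospective, so the change needs a dated amendment stating whether retention data had been seen. Success also becomes harder to claim. No new data collection is needed.

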#### Fidelity

The secondary outcome will be fidelity, defined as the degree to which an intervention was implemented as prescribed in the original protocol [41]. Fidelity is a key element to move treatments from the clinical lab to real-world delivery systems [42]. It can be measured through self-report, ratings, or direct observation. In this study, fidelity will be determined with an implementation form (Table 2), that will be filled by the two mindfulness instructors after the intervention is completed. A score below 40% will indicate low fidelity to the original protocol, a score between 40% and 70% will indicate moderate fidelity and a score higher than 70% will indicate high fidelity to the original protocol.

**Table 2 Tab2:** Implementation form

1. Did the family/patient sign the *Informed Consent Form*?	Yes/No
2. Was the family invited to get familiar with the program by accessing the online material available on the website?	Yes/No
3. Did the patient receive the graphic material before the first session?	Yes/No
4. Did the family/patient receive the password for online material before the first session?	Yes/No
5. Was the “task agreement” sent to the family before the first session?	Yes/No
6. Was the pre-test DASS answered right after the first session?	Yes/No
7. Were all sessions delivered on a video-conference platform?	Yes/No
8. Was the program delivered in 8 sessions, twice a week?	Yes/No
9. Did each session last between 30 and 60 min?	Yes/No
10. After 4 weeks, how many sessions had been delivered?	8 /less than 8
11. How many sessions did the patient miss during the program?	0/1/2/3/4/5/6/7/8
12. Was the program finished?	Yes/No
13. Was the post-test DASS answered right after the final session?	Yes/No
14. Was the program provided by a trained mindfulness instructor?	Yes/No
15. Where was the patient recruited to the program?	Inpatient unit/outpatient unit

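### The Table 2 form does not record whether session content was delivered, and without a stated scoring rule the fidelity category depends on assumptions

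*Protocol article*

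**What the plan says.** In the protocol article, the Fidelity section makes fidelity the secondary outcome, "defined as the degree to which an intervention was implemented as prescribed in the original protocol". It is measured with the implementation form in Table 2, "that will be filled by the two mindfulness instructors after the intervention is completed".

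Three bands are fixed: "A score below 40% will indicate low fidelity to the original protocol"; "a score between 40% and 70% will indicate moderate fidelity"; "a score higher than 70% will indicate high fidelity to the original protocol". The Data analysis section adds only this: "Fidelity will be classified according to the score measured by the implementation form".

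Table 2 has 15 items. Twelve are Yes/No (1-9, 12, 13, 14). Item 10 has two levels, eight sessions or fewer. Item 11 ("How many sessions did the patient miss during the program") runs from 0 to 8. Item 15 ("Where was the patient recruited to the program") takes inpatient or outpatient unit. The article gives no points per item and no denominator. It also does not say which items count.

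**The concern.** The outcome is meant to grade whether the programme was given as prescribed. What is prescribed is mainly the six modules of Table 1, delivered in sessions 2 to 7, and no item asks whether any of them was covered. An instructor could replace every module and still answer every item favourably.

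The rest of the form is weighted towards other things. Item 1 is consent, items 2-5 are set-up steps, and items 6 and 13 are questionnaire completion: seven items. Only items 8, 10, 11 and 12 record how much of the programme was given. Of these, 8 and 10 largely overlap, because eight sessions at two per week is eight sessions in four weeks. Item 15 describes the patient's route into the study and says nothing about fidelity.

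At stake is the meaning of a reported moderate or high fidelity. The article offers the study as a model for a later efficacy trial, and that trial would need to know whether the programme was actually delivered.

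**Working it through.** The plan gives no worked score to reproduce, so the check scores hypothetical patients under nine simple rules, one point per item unless stated, and applies the plan's bands.

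**Case 1, session 1 only.** Items 1-7, 9 and 14 are Yes (9 points). Items 8, 12 and 13 are No, item 10 is fewer than eight, and item 11 is 7 missed. By the Intervention content section, session 1 is introduction and guidelines; the modules start in session 2.

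**Case 2.** As case 1, but items 7 and 9 are No, because most sessions were not held (7 points).

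**Case 3.** As case 1, but 4 of 8 sessions held, so item 11 is 4 missed.

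| Rule | Case 1 | Case 2 | Case 3 |
|---|---|---|---|
| Yes/No items only | 9/12 = 75.0% high | 7/12 = 58.3% | 9/12 = 75.0% high |
| plus item 10 | 9/13 = 69.2% | 7/13 = 53.8% | 9/13 = 69.2% |
| plus item 11, all-or-none | 9/14 = 64.3% | 7/14 = 50.0% | 9/14 = 64.3% |
| plus item 11, proportional | 9.125/14 = 65.2% | 7.125/14 = 50.9% | 9.5/14 = 67.9% |
| item 11 all-or-none, item 15 = 0 | 9/15 = 60.0% | 7/15 = 46.7% | 9/15 = 60.0% |
| item 11 all-or-none, item 15 = 1 | 10/15 = 66.7% | 8/15 = 53.3% | 10/15 = 66.7% |
| item 11 as 0-8 points, no item 15 | 10/21 = 47.6% | 8/21 = 38.1% low | 13/21 = 61.9% |
| item 11 as 0-8 points, item 15 = 0 | 10/22 = 45.5% | 8/22 = 36.4% low | 13/22 = 59.1% |
| item 11 as 0-8 points, item 15 = 1 | 11/22 = 50.0% | 9/22 = 40.9% | 14/22 = 63.6% |

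Unmarked cells are moderate.

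- Case 1 ranges from 45.5% to 75.0%: moderate under eight rules, high under one, low under none.
- Case 2 ranges from 36.4% to 58.3%: moderate under seven, low under two.
- If item 6 is also No in case 2, the points fall to 6 and the range is 7/22 = 31.8% to 6/12 = 50.0%, low under three rules.
- Under the five rules that omit item 11 or score it all-or-none, 4 of 8 sessions scores exactly the same as 1 of 8.
- With no session held and only items 1-5 answered Yes, the range is 5/22 = 22.7% to 5/12 = 41.7%, low under seven rules (for example 5/15 = 33.3%).
- Full delivery scores 14/15 = 93.3% or 21/22 = 95.5% if item 15 sits in the denominator without credit, and 100% otherwise.

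**The case against.** The strongest reply is that this is a condensed article. Item weights, the denominator and the list of scored items may stand in a full protocol or form manual that is not shown, and item 15 may be a descriptive field printed on the same sheet. That stands as far as it goes: absent weights alone would be no finding. But a scoring key could not supply content items that the form lacks, nor could it make place of recruitment a measure of fidelity.

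Other replies also carry some weight. Checking that planned steps happened is a proper use of a fidelity form. The article names self-report as one accepted way to measure fidelity, and its Discussion concedes that fidelity may be overestimated, though it attributes this to extra effort. Standard videos and workbooks, trained instructors and supervision by the investigators support consistent content. They make wrong content less likely, but they do not record what was given.

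Three stronger readings are tempting, and the documents do not support them:

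- **That the plan rates a patient with 1 of 8 sessions as moderate.** A score without a stated rule fixes no rating. The result can be high (75.0%) or low (36.4%), depending on the rule and the answers assumed.
- **That the low band cannot be reached once set-up is done.** It can: set-up with no session is low under seven of the nine rules.
- **That patients who stop early will have no form.** Items 11 and 12 allow for missed sessions and an unfinished programme, so the form anticipates them. The completion time after the intervention leaves a risk of missing forms, not a certainty.

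**Conclusion.** The point holds in a limited form. Whatever the scoring rule, the form does not capture whether the prescribed content was delivered, and it contains one item with no faithful answer. As printed it yields no unique percentage. Under most simple rules a patient who received only the introductory session would not be classed as low: 45.5% to 75.0% if items 7 and 9 are Yes, 36.4% to 58.3% if they are No. These figures rest on the assumed rules and on the assumed answers, above all to items 6, 7 and 9.

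The consequence is confined to the secondary, descriptive fidelity category. The success rule in the Feasibility section uses recruitment, retention and participation only and is not affected. The form is worth correcting, but the primary conclusion does not depend on it.

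**What to change.** Revise Table 2 and state its scoring:

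- Take items 1, 6, 13 and 15 out of the score and keep them as descriptive data.
- Score only one of items 8 and 10.
- Score item 11 in proportion to sessions delivered.
- Add one yes/no for each of sessions 2-7: was the Table 1 content covered?
- State the denominator.
- Complete the form for every enrolled patient, including those who stop early.

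At one point per item this leaves 16 points: items 2-5, 7, 9, 14, one of 8 and 10, 11, 12, and six content items. Full delivery is 16/16 = 100%. With items 7 and 9 Yes, session 1 only scores (4 + 3 + 0.125)/16 = 44.5%. Sessions 1-4 with content covered score (4 + 3 + 0.5 + 3)/16 = 65.6%, so the two cases now separate. Session 1 only is still moderate at equal weights, because the set-up items keep 4 of 16 points. If the sponsor also reports items 2-5 apart, the same two cases score 3.125/12 = 26.0% and 6.5/12 = 54.2%. The sponsor should decide this when stating the denominator.

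The cost is a revised one-page form and a minute or two of instructor time per session. The study is already under way, so for patients already treated the content items would be retrospective or missing and should be reported as such.
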